### Standard care

The standard perioperative care programme is focused on supporting patients in adopting a new healthy lifestyle incorporating mental and physical health. The objectives of the programme are to provide guidance to enhance adherence to healthy lifestyle and behaviour changes, ensure understanding of the benefits of a healthy lifestyle and improve both physical and mental health. The programme is provided by a multidisciplinary team consisting of bariatric physicians, dietitians, psychologists, kinesiologists, surgeons and internists. The programme consists of group sessions with up to 10 patients per group; each group is assigned to one of the healthcare professionals who functions as coach. Preoperatively, patients participate in group sessions on a weekly basis for 4 weeks. Postoperatively, the group sessions are repeated every 3–6 weeks for a 15-month period. In addition, medical checks are performed by a bariatric physician at 3 weeks postsurgery and repeated every 3 months, up to 1 year post-MBS.

Allocation to our control group does not restrict participants from engaging in RT or consuming additional protein. This is emphasised by the research team during recruitment. Moreover, the research team is trained to ensure equipoise delivery during recruitment by presenting both study arms as equally important for the aim of this study.

### Intervention

The ENRICHED intervention consists of two consecutive phases, starting 3 weeks after surgery and continuing for a total of 24 weeks (figure 1). Phase 1 (3–14 weeks post-MBS) focuses on home-based and supervised RT and gradually increasing protein supplementation. Phase 2 (15–26 weeks post-MBS) continues with the same RT protocol while transitioning from protein supplementation to enhancing dietary protein intake.

#### Resistance training

##### Standard care

As part of the standard perioperative care programme, patients are provided with a semistructured home-based RT protocol, which can be performed using little to no equipment. This home-based RT protocol includes three difficulty levels with six different whole-body RT exercises. Patients are advised to perform 2–3 weekly RT sessions on non-consecutive days. Each exercise is completed after three sets of 6–12 repetitions, with 60 s of rest between sets. Patients are advised to progress to a higher difficulty level once they are able to perform three sets of 12 repetitions at the current difficulty level.

##### Intervention: home-based and supervised RT

Patients in the intervention group will receive an adapted version of the home-based RT protocol that is part of the standard care. This adapted protocol includes four difficulty levels with six adjusted whole-body RT exercises to ensure activation of all major muscle groups (online supplemental table 1). In the intervention protocol, each exercise is completed after four sets of 8–12 repetitions, with 60 s of rest between sets. All exercises in the home-based RT protocol can be performed using no to little equipment to ensure an easy translation to the home environment.

As part of the intervention, weekly RT sessions are provided at the clinic and are supervised by an experienced kinesiologist. The supervised RT protocol includes four machine-based whole-body exercises and one exercise using body weight (online supplemental table 2A). During the first supervised session, the kinesiologist will guide patients through the home-based RT protocol to ensure they understand how to perform the home-based exercises correctly and safely. During the second supervised session, patients are familiarised with the exercises of the supervised RT protocol and the one repetition maximum (1-RM) will be assessed for each exercise. If the kinesiologist considers that a reliable 1-RM assessment cannot be performed in a participant, the participant is instructed to perform the exercises based on perceived exertion using the 6–20 Borg rating of perceived exertion scale.^21^ Patients are familiarised with the scale before enrolment to RT. All participants are instructed to train at a Borg score between 12 and 14, corresponding to ‘somewhat hard’. During the following sessions, the prescribed training scheme (online supplemental table 2B) serves as a basis, progressing from three sets of 10–14 repetitions at 60% of the 1-RM to three sets of 8–10 repetitions at 75% of 1-RM. Adjustments to this scheme can be made according to the Borg scores to ensure that participants consistently train within the target range of Borg scores 12–14. Each set of exercises is performed with a lifting cadence of 1 s concentric and 1 s eccentric contraction with 60 s of rest between each set.^22^ During the 12th session, the 1-RM will be reassessed to prescribe RT for the remaining sessions.

### Protein intake

#### Standard care

As part of the multidisciplinary standard care, patients receive dietary guidance from dieticians. All patients are provided with examples of a balanced daily dietary intake to meet all essential macronutrient and micronutrient requirements.

#### Intervention: protein supplementation

3 weeks post-MBS, patients will start with consumption of 20 g of whey protein once a day for 4 weeks, followed by 20 g of whey protein two times per day for the next 4 weeks and finally 20 g of whey protein three times a day for the last 4 weeks (figure 1). The whey protein supplement (Nutri Whey ProHeat, Friesland Campina, Amersfoort, the Netherlands) is a heat-stable whey protein derived from cheese whey which is concentrated to an 83% protein content. The protein supplement is provided as a powder which is soluble in fluids. To support adherence and manage tolerability, counselling sessions with a dietician are scheduled every 3–4 weeks during this phase.

#### Intervention: dietary protein intake

In the second phase, the focus for the dietary protein intake shifts from protein supplementation to enhancing dietary protein intake of minimally 60 g/day. To support and promote a long-lasting incorporation of sufficient protein intake into the daily dietary intake pattern, additional counselling sessions with a dietician will be scheduled every 2–4 weeks during this phase. Additionally, participants will be provided with examples of dietary adjustments. A total of six counselling sessions with a dietician will be provided to support patients with translating these changes into their daily routine.

### Follow-up

After the 6-month intervention period, all participants in the intervention group will continue with the standard care programme. During the 6-month follow-up period, no additional counselling sessions with the dieticians, nor supervised RT sessions will be provided.

### Outcome measures

The primary outcome is the difference in proportion of patients with disproportional FFML/TWL (ie, ≥30%) in the intervention group compared with the control group at 3 months post-MBS. Secondary outcomes are postintervention differences in body composition, muscle strength and function, cardiorespiratory fitness, (cardio)metabolic health, HRQoL, gastrointestinal discomfort, cost-effectiveness of the intervention and treatment satisfaction in the intervention group. Most outcomes are measured preoperatively and at 3, 6 and 12 months post-MBS. Cost data are assessed preoperatively and at 6 and 12 months post MBS, and treatment satisfaction is assessed after the 6-month intervention period. Cost and outcome data are used to calculate the incremental cost-effectiveness of the intervention in terms of cost per successfully treated patient using a time horizon of 1 year.

The primary outcome was set at 3 months post-MBS as previous studies have shown that the most pronounced changes in body composition, including substantial reduction in FFM, occur during this early postoperative phase.^5 23^ Our intervention, combining RT and protein supplementation, was specifically designed to target this critical period. Secondary outcomes will be assessed at 6 and 12 months to assess the persistence of potential effects over time.

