	Regular physical activity	Do you carry out light/moderate/vigorous physical activity on a regular basis (yes/no); if yes: how many days a week do you carry out light/moderate/vigorous physical activity (days/week); and: on those days, how many min a day do you do light/moderate/vigorous physical activity (min/day)?
	Previous GLP-1 use	Have you previously used GLP-1 medication (yes/no); if yes: which type of GLP-1 medication have you used (liraglutide (Saxenda)/semaglutide (Ozempic/Wegovy)/tirzepatide (Mounjaro)/I do not know); and: for how long did you use this medication (months); and: how much weight did you lose while using this medication (kg)?
	Healthcare consumption	In the past 3 months, have you had one or more appointments with any of the following healthcare providers (general practitioner/medical specialist/paramedical healthcare provider (please specify)/none of the above); if yes: how many appointments have you had in the past 3 months; in the past 3 months, have you visited a hospital or another type of healthcare facility (no/yes, a hospital/yes, another type of healthcare facility (please specify); if yes: what was the purpose of your visit (day treatment/inpatient admission/outpatient consultation); if ‘inpatient admission’: how many days were you admitted to the hospital or healthcare facility (days); did you undergo a medical procedure during your visit (yes/no)?
	Patient-reported health	Mobility (I have no/slight/moderate/severe problems walking or I am unable to walk); ability to wash or dress yourself (I have no/slight/moderate/severe problems washing or dressing myself or I am unable to wash or dress myself); ability to perform your daily activities (I have no/slight/moderate/severe problems performing my daily activities or I am unable to perform my daily activities); level of pain or discomfort (I have no/slight/moderate/severe/extreme pain or discomfort); emotional state (I am not/slightly/moderately/severely/extremely anxious or depressed).

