### Cost-effectiveness

As part of the ENRICHED trial, a cost-effectiveness analysis will be performed, focusing on formal care costs over a period of 12 months. These costs will include routine costs of standard perioperative care, intervention costs (eg, protein supplementation, RT equipment and personnel) and general healthcare consumption costs. Healthcare consumption will be assessed using extracted data from the electronic patient records, supplemented by selected items from the iMTA Medical Consumption Questionnaire.^37^ Additionally, HRQoL will be assessed using the EQ-5D-5L questionnaire.^32^ The incremental costs between the intervention and standard care will be related to the difference in proportion of patients achieving the success criterion defined as FFML/TWL ≥30% at 12 months.

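### The healthcare-use questions, with 3-month recall at 6 and 12 months, leave months 0–3 and 6–9 unasked, so self-reported care not held in the records is missed for half of the 12-month horizon

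*Protocol article*

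**What the plan says.** Under Outcome measures, the protocol article sets the general schedule ("Most outcomes are measured preoperatively and at 3, 6 and 12 months post-MBS") and then gives costs a shorter one: "Cost data are assessed preoperatively and at 6 and 12 months post MBS". The result is to be expressed as "cost per successfully treated patient using a time horizon of 1 year".

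The Cost-effectiveness section describes an analysis "focusing on formal care costs over a period of 12 months". It names three components: routine perioperative care, intervention costs, and "general healthcare consumption costs". On the source of the third it says: "Healthcare consumption will be assessed using extracted data from the electronic patient records, supplemented by selected items from the iMTA Medical Consumption Questionnaire".

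The items themselves are in Table 2 (Data management), in the healthcare consumption row. Both stems have the same look-back. One reads "In the past 3 months, have you had one or more appointments with any of the following healthcare providers" and the other "in the past 3 months, have you visited a hospital or another type of healthcare facility". The answer options include general practitioner, medical specialist, paramedical provider, hospital and other facility.

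The article gives no longer recall period and no cost questionnaire at 3 or 9 months.

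**The concern.** A 3-month recall captures a full year only if the question is asked every 3 months. Here it is asked at two postoperative points that are 6 months apart, so the recall window and the schedule do not fit the stated horizon.

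The investigators chose to supplement the records with a questionnaire, which implies that they expect the records alone to be incomplete. That supplement then operates for only half of the period it is meant to complete.

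The position of the gap matters as well as its length. Months 0–3 contain recovery from surgery and the start of supervised training and protein supplementation. The Discussion names gastrointestinal discomfort as a possible reason for low compliance in earlier studies. If the arms differ in outside care at any time, this is a plausible period. An analysis plan can later choose how to fill unasked months, but it cannot recover reports that were never collected.

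**Working it through.** The article states no coverage figure, so there is none to reproduce. Coverage can be counted directly.

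**Inputs.** Cost assessments before surgery and at months 6 and 12 (Outcome measures); recall of 3 months for both stems (Table 2); horizon of months 0–12 (Outcome measures, Cost-effectiveness); phase 1 from week 3 to week 14 (Intervention), with 4 + 4 + 4 = 12 weeks of supplementation (Intervention: protein supplementation).

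**Coverage.** An assessment at month v with recall r covers months v − r to v.

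- Before surgery: −3 to 0, outside the horizon.
- Month 6: 6 − 3 = 3, so months 3–6.
- Month 12: 12 − 3 = 9, so months 9–12.
- Covered: 3 + 3 = 6 of 12 months (50%). Not asked: months 0–3 and 6–9, also 6 of 12 (50%).

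**Overlap with the intervention.** Three months is about 52/4 = 13 weeks. Supplementation starts at week 3, so about 13 − 3 = 10 of the 12 weeks of phase 1 fall in the first unasked window.

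**Effect of filling the gap.** Let q1 to q4 be the mean cost per quarter, in one arm, of care known only by self-report. The questionnaire observes q2 and q4.

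- True total: q1 + q2 + q3 + q4.
- Scaled by 12/6 = 2: 2(q2 + q4). Error: (q2 + q4) − (q1 + q3).
- Unasked months entered as zero: q2 + q4. Error: −(q1 + q3).

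The same expressions hold for the between-arm difference, with quarterly differences in place of quarterly means. Scaling has no error when the unasked quarters match the asked ones, as they do under constant use. If q1 is high relative to the later quarters, scaling understates the total. The article gives no values for q1 to q4, so the error has no derivable size.

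**Coverage under alternatives.**

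| Schedule | Months asked about | Coverage |
|---|---|---|
| As written: 6 and 12, recall 3 | 3–6, 9–12 | 6/12 = 50% |
| Add the 3-month visit, recall 3 throughout | 0–6, 9–12 | 9/12 = 75% |
| Add the 3-month visit, recall 6 at month 12 | 0–3, 3–6, 6–12 | 12/12 = 100% |
| 6 and 12 only, recall 6 | 0–6, 6–12 | 12/12 = 100% |

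**The case against.** The strongest reply is that the questionnaire is not the main source. The Cost-effectiveness section puts the electronic patient records first, and nothing limits their extraction to 3-month windows. Routine and intervention costs do not rest on patient recall at all. This stands, and it confines the point to one supplementary source within one of three cost components. A reader might infer that the whole 12-month cost difference rests on half a year of data; the article does not support that.

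A reader might also infer that questionnaire-based costs and their arm difference would be halved. That follows only if use is constant and unasked months are entered as zero. The article does not say they would be, and under constant use simple scaling recovers both quantities.

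Nor is it shown that general practitioner, paramedical or other-facility care is lost. The article does not say which records are extracted or what they contain, so the claim has to stay conditional.

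Three further replies carry less weight.

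- Table 2 does not tie the items to visits, so they might also be asked at 3 months. That would contradict Outcome measures, which separates cost data from the outcomes measured at 3 months, and months 6–9 (25%) would still be unasked.
- Patients are in close contact with the clinic in the first 3 months through medical checks, supervised sessions and dietician counselling. That helps to detect complaints, but it does not cost care obtained elsewhere.
- Short recall at spaced visits, with interpolation, is a recognised compromise with recall error, and the filling rule may sit in a document not shown. Its absence here is therefore not held against the article. But interpolation needs observations on both sides of a gap, and months 0–3 have no postoperative observation before them.

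**Conclusion.** The point holds in a limited form. The healthcare-consumption questions do not ask about months 0–3 and 6–9, which is 6 of the 12 months in the horizon. The 50% is the time coverage of one instrument. It is not a share of missing costs and not an estimate of bias.

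The consequence depends on two things the article does not settle: how much of the self-reported care is absent from the extracted records, and how far use in the unasked months differs from use in the asked ones. If the records hold all such care, little is lost. If they do not, the estimate leans on an assumption of roughly constant use, which is doubtful for months 0–3.

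Cost-effectiveness is a secondary outcome, and the primary endpoint is unaffected. The change is still worth making, because it is cheap and the data cannot be collected reliably afterwards.

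**What to change.** Ask the healthcare-consumption items at the existing 3-month visit as well, where structured questions are already put in person (Questionnaires section). This covers months 0–3. Keep the 3-month recall at month 6, for months 3–6. At month 12, choose one of two options and state it:

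- use a 6-month recall, for months 6–12, which gives full coverage; or
- keep the 3-month recall and state that months 6–9 are interpolated from the adjacent windows. The remaining error is then (q2 + q4)/2 − q3, in one later quarter only.

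Amend the cost schedule under Outcome measures to match, and show the visits and recall periods for these items in Table 2.

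Recruitment began in May 2025 and is expected to run until December 2026, so some participants may already be past the 3-month visit. For them, either rely on the records and report the months 0–3 self-report as missing, or ask once with an extended recall.

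The cost is a form change and a few minutes at one visit. With the 6-month recall there is also some added recall error, and windows of different length within one outcome; the one-off extended recall would add a further format.

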### Measurements

#### Anthropometrics and body composition

Body height and weight will be measured during each measurement visit, using a stadiometer (BSM 170B, InBody, Seoul, South Korea) and will be reported to the nearest 1 mm. Body weight (kg) will be measured using a bioelectrical impedance machine (InBody 770, Seoul, South Korea).^24^ Both measurements will be used to calculate BMI (kg/m^2^). Waist circumference (cm) will be measured midway between the lower rib margin and iliac crest.

Body composition will be assessed in the entire study population by bioelectrical impedance analysis (BIA) (InBody 770, Seoul, South Korea), which can distinguish between FM and FFM. BIA is a validated, low-cost and readily available technique for assessing body composition changes in longitudinal study designs.^25^ Weight loss, FM loss and FFML between preoperative and follow-up assessments will be determined, and the FFML/TWL will be calculated as the absolute FFML (kg) divided by TWL (kg) × 100%.

DXA measurements (Hologic Horizon A, Marlborough, Massachusetts, USA) will be performed in the subgroup (n=100) before and 3 months after surgery, as this is considered the gold standard for measuring body composition. Within the same subgroup, an additional BIA measurement using a different device (TANITA DC-360, Amsterdam, the Netherlands) will be conducted to validate the different methods of body composition assessment.

#### Muscle strength and physical performance

Maximum strength (kg) will be assessed to the nearest 0.1 kg using a leg extension machine (Leg Extension Rev, Technogym, Cesena, Italy) by performing a single repetition isometric strength test. Additionally, a six-repetition maximum power (Watt) test will be performed to assess maximum power to the nearest 0.1 Watt and to assess maximum power acceleration (deg/s) to the nearest 0.1 deg/s.

Maximal handgrip strength (kg) will be assessed to the nearest 0.1 kg using a hand size adjusted dynamometer (InGrip Hand Dynamometer, InBody, Seoul, South Korea). The measurement will be conducted alternately with both arms, twice for each arm, with ±10 s rest between measurements. The maximum strength is defined as the maximum value (kg) of the two measurements for each arm.

The Short Physical Performance Battery (ie, a short balance, walking and chair-rise test) will be performed to determine functional capacity.^26^

In the subgroup (n=100), habitual PA patterns will be assessed using ActivPAL (ActivPAL3 micro, PAL Technologies, Glasgow, UK),^27^ a small device (25×45×5 mm) attached to the participant’s thigh using hypoallergenic tape and sealed for waterproof protection. ActivPAL combines a triaxial accelerometer with an inclinometer which can accurately distinguish between sitting, standing and walking.^28^ Participants will be instructed to wear the ActivPAL for 24 hours/day for 8 consecutive days following each measurement visit. Raw ActivPAL data will be extracted using PAL Software Suite V.9 (Pal Technologies, Glasgow, UK) and analysed using the ActiPASS data processing software^29^ to determine time spent in light PA (ie, metabolic equivalent of a task (MET)-value <3), and moderate-to-vigorous PA (ie, MET-value ≥3).^27 30^

#### Cardiorespiratory fitness

Cardiorespiratory fitness (defined as maximum oxygen uptake (VO_2_ max)) will be assessed using the Åstrand test, a 6 min submaximal cycle ergometer test, which is preceded by 2 min of warming-up. During this test, the participant will be instructed to aim for 50–60 rotations per minute while the resistance of the cycle ergometer will be increased every 30 s until a heart rate (HR) of ∼120 bpm is reached. Resistance will be increased a maximum of four times within the first 2 min of the test. When the aimed HR is reached, the participant will be instructed to continue cycling at this resistance level for the remainder of the test. The VO_2_ max will be estimated by combining the achieved maximum output and HR from the last minute of the test.

#### Blood sampling

Fasted venous blood samples will be drawn from an antecubital vein preoperative, and 3, 6 and 12 months postoperative, to provide information on fasting glucose and insulin, glycated haemoglobin, lipid profile and high sensitive C reactive protein (hs-CRP). The blood will be collected in serum tubes (serum separator tubes, SSTII advance, BD Vacutainer, Becton Dickinson, Franklin Lakes, New Jersey, USA), lithium-heparin plasma tubes (plasma separator tubes, LH PSTII, BD Vacutainer) and EDTA tubes (K2E, BD Vacutainer). The serum tubes and the lithium-heparin plasma tubes will be centrifuged according to the manufacturer’s instructions. From the EDTA tubes, whole blood samples will be collected. Aliquots will initially be stored at −20°C at the research sites and will be transferred within 4 weeks to the Radboudumc for long-term storage at −80°C.

